### Data analysis

To evaluate therapeutic approaches to HCC in China, the number and percentage of patients using each treatment (plus any new treatments that are approved and used within the study period) will be determined for each study year, in total and stratified by disease stage and site. Treatment patterns will also be assessed by disease stage for each study year. Patient characteristics will be stratified by disease stage and by site for each study year.

To assess therapeutic outcomes, age- and gender-adjusted rates will be calculated for each study end point. Cox proportional hazard models will be used for the time-to-event end points (overall survival and disease progression) to determine hazard ratios for each treatment approach, and Kaplan-Meier curves will be generated. Logistic regression models will be used for categorical end points (treatment-limiting adverse events and treatment failure). Covariates for the models will include disease stage, gender, age, duration of disease, etiology of disease, liver status, tumor size/spread, surgical intervention/number of interventions, and number of comorbidities; analyses will be conducted at the site and country level. The same analysis plan will be adopted for the evaluation of survival and other clinical end points with sorafenib versus other therapies, except that "treatment" will be included as a covariate. Further analyses will be conducted to evaluate clinical characteristics and demographics of patients treated with sorafenib versus other treatments for HCC. In addition, data collected will be used to analyze additional aspects related to HCC epidemiology and management in China (Table 2). All tests of statistical significance will be carried out at the 0.05 level.

**Table 2 T2:** Additional aspects of HCC management for potential evaluation using data from the HCC BRIDGE China national study.

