## Methods

### Study design

The global HCC BRIDGE study is a multiregional longitudinal cohort trial including patients diagnosed with HCC from January 1, 2005, to June 30, 2011 [10]. Patients enrolled in the study will be followed from the date of HCC diagnosis to December 31, 2011, or date of death, whichever comes first. The HCC BRIDGE China national study comprises the portion of the global HCC BRIDGE study conducted within mainland China. To ensure that the national study is geographically representative, it was designed to include patients enrolled at sites from all 7 traditional regions across China (North, North-East, East, South, South-West, North-West, and Central).

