**Primary end point**
Overall survival
Number of days from date of treatment initiation to date of death. Death will be verified by sites based on death certificates or via caregiver, relative, or health care provider, and death information source will be captured in data collection. Surviving patients will be censored from last date of treatment assessment.

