### Sample size

Sample size requirements for the Chinese regional sites are approximately 200 patients per site per year between 2008 and 2010 (plus approximately 192 per site for the first 6 months of 2011) to capture current treatment and clinical outcomes in HCC, and 100 patients per site between 2005 and 2007 for historic controls. Pooling of data across all sites in China will be employed to describe disease and treatment characteristics across the country.

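### Survival curves and per-treatment Cox models carry no diagnosis period, yet only 2005-2007 patients can be at risk after year 4, so late pooled estimates are unbiased only if prognosis did not change between periods

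*Protocol article*

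**What the plan says.** Under Study design, the cohort consists of "patients diagnosed with HCC from January 1, 2005, to June 30, 2011", each "followed from the date of HCC diagnosis to December 31, 2011, or date of death, whichever comes first". Table 1 counts overall survival as "Number of days from date of treatment initiation to date of death", and "Surviving patients will be censored from last date of treatment assessment".

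The Sample size section sets per-site quotas of about 200 a year for 2008 to 2010, about 192 for the first half of 2011, and "100 patients per site between 2005 and 2007 for historic controls".

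The Data analysis section reports treatment use, treatment patterns and patient characteristics for each study year. For outcomes it plans Cox models "to determine hazard ratios for each treatment approach, and Kaplan-Meier curves will be generated", lists nine covariates, none of them diagnosis year or period, and adds that "analyses will be conducted at the site and country level". It sets no time horizon for the curves. Separately, Comparator groups plans to compare outcomes between 2005-2007 and 2008-2011 for the sorafenib question.

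**The concern.** One closing date means that a patient's longest possible follow-up is fixed by the date of diagnosis. Kaplan-Meier and Cox methods handle this without bias as long as prognosis does not depend on that date. A study that compares outcomes before and after a new drug became available cannot take this for granted.

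If later patients do better or worse, a curve pooled over diagnosis years takes its early part mostly from 2008-2011 patients and its slope after year 4 entirely from 2005-2007 patients. The late cumulative figure then describes neither period and not their mixture either. Overall survival is the primary end point, and the planned curves would carry this distortion without showing it.

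**Working it through.** **1. Longest follow-up by diagnosis date** (31 December 2011 minus diagnosis date)

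| Diagnosed | Days | Years |
|---|---|---|
| 1 Jan 2005 | 2555 | 7.0 |
| 31 Dec 2007 | 1461 | 4.0 |
| 1 Jan 2008 | 1460 | just under 4 |
| 31 Dec 2010 | 365 | 1.0 |
| 30 Jun 2011 | 184 | 0.5 |

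Survival is counted from treatment initiation and survivors are censored at the last treatment assessment. Later treatment or earlier last assessment only shortens these times, so the 4-year limit for 2008 onwards stands.

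**2. Share of the quotas diagnosed in 2005-2007**

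- Later patients per site: 3 × 200 + 192 = 792.
- If 100 is a total: 100 / (100 + 792) = 100/892 = 11.2%.
- If 100 is per year: 300 / (300 + 792) = 300/1092 = 27.5%.

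The quotas do not reproduce the stated population of about 9000: 15 × 892 = 13,380 and 15 × 1092 = 16,380. That is a separate matter, but it means the shares rest on the quotas as written.

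**3. What a pooled curve estimates.** The article gives no survival figure to reproduce, so the survival inputs are assumptions: exponential survival, treatment at diagnosis, uniform entry within each quota period, censoring only at the closing date, a 24-month median in 2005-2007 (hazard λ = ln 2 / 2 = 0.3466 per year), and a hazard of HR × λ from 2008.

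In large samples the pooled hazard at time t (years) is

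h(t) = Σ n·G(t)·S(t)·λ / Σ n·G(t)·S(t), and pooled S(t) = exp(−∫h),

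summed over the three entry groups. G(t) is the fraction of a group that can be followed to t, limited to the range 0 to 1: (7−t)/3 for 2005-2007, (4−t)/3 for 2008-2010, and (1−t)/0.5 for 2011. The true mix is the quota-weighted average of the two survival functions. With n = 100, 600 and 192, survival at 5 years is:

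| HR, later vs earlier | Pooled | True mix | 2005-2007 | 2008-2011 | Pooled minus mix (points) |
|---|---|---|---|---|---|
| 1.0 | 17.7% | 17.7% | 17.7% | 17.7% | 0 |
| 0.9 | 19.6% | 20.7% | 17.7% | 21.0% | −1.1 |
| 0.8 | 21.8% | 24.2% | 17.7% | 25.0% | −2.4 |
| 0.7 | 24.3% | 28.4% | 17.7% | 29.7% | −4.1 |
| 0.6 | 27.2% | 33.4% | 17.7% | 35.4% | −6.2 |

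At HR 0.7 the pooled curve is already 2.1 points low at year 4 (34.4% against 36.4%). From there it falls at the 2005-2007 rate: 24.3/34.4 = 0.707, where 2008-2011 patients would have exp(−0.7 × 0.3466) = 0.785.

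**4. Sensitivity.** If 100 is per year, the gaps for HR 0.9 to 0.6 are again 1.1 to 6.2 points. With a 12-month median (100 as a total) they are 0.4 to 3.7 points.

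**5. Numbers at risk per site** (24-month median, 100 as a total): 100 × 0.25 = 25 at year 4. At year 5, two thirds of the group can still be followed, so 100 × 2/3 × 0.177 = about 12. Both are before any split by treatment.

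**6. Hazard ratios.** In simulations with medians of 0.5, 1 and 2 years, HRs of 1.0, 0.8 and 0.6, and both readings of the quota, events after year 4 were 0.04% to 5.6% of all events.

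**The case against.** The strongest answer is that the article never says the curves merge all diagnosis years. The only pooling it states is across sites. The Sample size section assigns 2008-2011 patients to current outcomes and 2005-2007 patients to historic controls, Comparator groups plans a split by period, and a full analysis plan could add strata or a time horizon. This stands as far as it goes: pooling over years is an inference. It is a reasonable one, because the same section names study year for the descriptive tables and then names other levels, and covariates without period, for the outcome models.

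Four stronger readings are tempting and not supported:

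- *Every pooled survival figure beyond 4 years rests on 2005-2007 patients alone.* Cumulative survival at 5 years contains survival to year 4, to which all patients contribute. Were the reading true, the pooled 24.3% at HR 0.7 would equal the 17.7% of 2005-2007. Only conditional survival after year 4 rests on that group alone.
- *The treatment hazard ratios are driven by the late tail.* They draw almost all their information from the first 4 years. Their weakness is the missing period term.
- *The study presumes that outcomes differ between periods.* It says only that they will be compared.
- *Staggered entry with one closing date is itself a flaw.* Without a trend the pooled estimate is unbiased.

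It is also fair that the calculation applies one hazard change to everyone and has no treatment dimension. Survival within a given treatment may have changed less, and the sorafenib curve hardly mixes periods at all.

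**Conclusion.** The point holds as a conditional one. It is certain from the stated dates that only 2005-2007 patients, 11% or 27% of the quotas, can be at risk after year 4, and that the listed outcome models have no diagnosis period. It is conditional that late pooled estimates are biased: this needs curves pooled over diagnosis years and a change in prognosis between periods. Under the assumed 24-month median and hazard ratios of 0.9 to 0.6, pooled 5-year survival is about 1 to 6 points too low for the true mix. If later patients fared worse, the bias would run the other way. No survival input comes from the article, and the sizes are for all treatments together. This is an inexpensive improvement to the analysis, not an error that undermines the study.

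**What to change.** In the Data analysis section, state that:

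- overall survival and progression curves will be drawn separately for patients diagnosed in 2005-2007 and in 2008-2011;
- the 2008-2011 curves will end at 4 years;
- the general per-treatment Cox models will have a baseline hazard stratified by these two periods.

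State also that the stratum does not apply to the comparison of sorafenib with historic controls. There treatment and period largely coincide, so stratifying by period would remove most of the planned contrast. Because Comparator groups separates its periods by each site's first record of sorafenib use, the text should say that the strata here are defined by diagnosis date.

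The diagnosis date is already collected, so no new data are needed. The cost is more curves, visibly less precise tails for 2005-2007, and no survival estimate beyond 4 years for 2008-2011 patients, for whom the data hold none.

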### Comparator groups

In order to evaluate the influence of sorafenib on HCC treatment patterns in China, clinical outcomes will be compared across 2 periods within the overall study duration: (1) the period when sorafenib was unavailable (2005 to 2007) and (2) the period when sorafenib was available for use (2008 to 2011). These 2 periods will be differentiated by the first record of sorafenib use at each site. Patients treated during the period when sorafenib was not available will act as historic controls and will be statistically matched within the pool of patient data by age, sex, Child-Pugh status, and HCC stage to patients treated with sorafenib between 2008 and 2011. Patients treated with non-sorafenib therapies during the period when sorafenib was available will act as concurrent controls and will be used to evaluate characteristics of HCC patients treated with sorafenib versus other therapies. In this study, "sorafenib treatment" is defined as the use of either sorafenib alone or concomitant use of sorafenib and other pharmacologic agents or interventions within 21 days of each other.

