**Secondary end points**
Disease progression
Number of patients by treatment intervention with MRI/CT evidence of visible arterial enhancement, radiologic report of progression, or radiologic report of new tumor growth or symptomatic/clinical progression.
Time to disease progression
Number of days from date of treatment initiation to date of documented disease recurrence based on MRI or CT by treatment intervention, or symptomatic/clinical progression. Patients without recurrence will be censored from last date of treatment assessment.
Complication rate
Number of patients by treatment intervention who were withdrawn due to adverse events prior to introduction of other therapy.
Time to treatment-limiting adverse events
Number of days from first date of treatment to date of withdrawal due to adverse event(s) prior to introduction of other therapy. Patients without treatment-limiting adverse events will be censored at last date of treatment assessment.
Treatment failure rate
Number of patients by treatment intervention with a finding of treatment switch, HCC-related hospitalization and emergency room visit, disease recurrence, or death prior to introduction of other therapy.
Time to treatment failure
Number of days to first treatment failure overall and by individual item. Patients without treatment failure will be censored from last date of treatment assessment.

CT, computed tomography; MRI, magnetic resonance imaging.

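### Ever/never logistic models for treatment failure and treatment-limiting adverse events leave the historic-control comparison confounded by unequal follow-up

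*Protocol article*

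**What the plan says.** The Data analysis section of the protocol article divides the end points between two models. On one side: "Cox proportional hazard models will be used for the time-to-event end points (overall survival and disease progression"). On the other: "Logistic regression models will be used for categorical end points (treatment-limiting adverse events and treatment failure"). The same plan is then applied to sorafenib versus other therapies, with treatment added as a covariate.

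Table 1 gives each of the two logistic end points in two forms:

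- a count of patients with the event, with no time window (complication rate, treatment failure rate);
- a time to the event, with a censoring rule. For treatment failure: "Patients without treatment failure will be censored from last date of treatment assessment". For treatment-limiting adverse events: "Patients without treatment-limiting adverse events will be censored at last date of treatment assessment".

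Under Study design, the cohort is "patients diagnosed with HCC from January 1, 2005, to June 30, 2011", and patients "will be followed from the date of HCC diagnosis to December 31, 2011, or date of death, whichever comes first". The Comparator groups section compares clinical outcomes between "the period when sorafenib was unavailable (2005 to 2007") and 2008 to 2011. Historic controls are matched to sorafenib patients on age, sex, Child-Pugh status and HCC stage.

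**The concern.** An ever/never outcome depends on the risk of the event and on how long the patient was watched. Logistic regression counts a patient censored event-free at six months as a non-event, exactly like one who was event-free at six years. That does little harm when the compared groups have similar follow-up. Here a common closing date gives the earlier group much longer follow-up by design, and no window, offset or follow-up term is stated to correct for it. The limitations in the Discussion do not mention it either.

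The study sets out to evaluate the influence of sorafenib. An artefact that makes the sorafenib period look better on treatment failure and tolerability could be read as a treatment effect.

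**Working it through.** **Plan's own figure.** The article gives no event rate, effect size or power for these end points, so there is nothing to reproduce. The hazards below are assumptions, shown as ranges.

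**Step 1: potential follow-up (Study design, Comparator groups).**
- Diagnosed 1 January 2005 to 31 December 2007: 7.0 down to 4.0 years to 31 December 2011. If diagnoses are spread evenly, the mean is 5.5 years.
- Diagnosed 1 January 2008 to 30 June 2011: 4.0 down to 0.5 years. With the per-site quotas in Sample size (200, 200 and 200 for 2008 to 2010, then 192 for the first half of 2011), the mean is [200 × (3.5 + 2.5 + 1.5) + 192 × 0.75] / 792 = 1644 / 792 = 2.08 years.

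The two ranges meet only at 4 years.

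**Step 2: treatment failure with no true difference.** Take one constant hazard λ in both periods. For follow-up spread evenly from a to b, the event-free proportion is S(a,b) = [exp(−λa) − exp(−λb)] / [λ(b − a)].

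At λ = 0.5 per year:
- 2005–2007: S(4,7) = (0.1353 − 0.0302) / 1.5 = 0.070, so 93.0% fail.
- 2008 to mid-2011: S(3,4) = 0.176, S(2,3) = 0.289, S(1,2) = 0.477, S(0.5,1) = 0.689. The quota-weighted mean is [200 × (0.176 + 0.289 + 0.477) + 192 × 0.689] / 792 = 0.405, so 59.5% fail.
- Odds ratio, later versus earlier: (0.595 / 0.405) / (0.930 / 0.070) = 0.11.

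With λ = ln 2 / median:

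| Median time to failure | 2005–2007 | 2008 to mid-2011 | Odds ratio (truth 1) |
|---|---|---|---|
| 0.5 years | 99.9% | 86.8% | 0.006 |
| 1 year | 97.4% | 69.6% | 0.06 |
| 2 years | 84.5% | 48.0% | 0.17 |
| 3 years | 71.4% | 36.2% | 0.23 |
| 5 years | 53.0% | 24.2% | 0.28 |

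With 1500 patients per group (15 sites × 100 historic controls, and an equal later group by assumption), a two-sided test at 0.05 rejects with probability about 1.00 in every row. At a 1-year median, a true hazard ratio of 1.5 against the later period still gives an odds ratio of 0.11, so the direction is reversed.

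**Step 3: treatment-limiting adverse events with no true difference.** The event must precede other therapy, so the patient leaves the risk period at switch or death. If a share s of the total exit hazard k is adverse-event withdrawal, the event proportion is s × [1 − S], with S computed at k. For s = 0.1 to 0.3:

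| Median on-treatment window | Odds ratio (truth 1) | Rejection probability, 1500 per group |
|---|---|---|
| 0.25 years | 0.95–0.96 | 5–10% |
| 0.5 years | 0.82–0.86 | 24–67% |
| 1 year | 0.64–0.69 | 79–100% |
| 2 years | 0.50–0.55 | 98–100% |
| 5 years | 0.41–0.44 | 98–100% |

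**Step 4: sensitivity to loss to follow-up.** The figures in Step 2 assume follow-up to the closing date. Add random loss at rate c, equal in both periods, with k = λ + c and s = λ / k. At λ = 0.5:
- c = 0.2 per year: 69.6% versus 49.9%, odds ratio 0.43.
- c = 0.5 per year: 49.7% versus 39.8%, odds ratio 0.67.

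Loss reduces the distortion but does not remove it.

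**Step 5: does anything in the plan correct for it?** Matching is on four baseline variables, none of which is time at risk. The covariates include duration of disease, which is not defined. Even if it meant time since diagnosis, it would not be time at risk from treatment start. The age- and gender-adjusted rates have no stated denominator and do not alter the logistic models.

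**The case against.** **Table 1 and the models do not contradict each other.** A reader might infer that Table 1 defines both end points only as censored times, so that logistic regression conflicts with the definition. It does not: Table 1 also gives count forms, and logistic regression fits those. What stands is narrower. The count forms have no time window, and the Data analysis section names no model for the time-to forms. The full protocol or SAP may name one, but the article has already fixed logistic regression for these two end points.

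**The 4–7 versus 0.5–4 year split is approximate.** It is an administrative maximum from diagnosis. Death, loss to follow-up and trial entry shorten it, and the period boundary is each site's first recorded sorafenib use. The planned comparison is also matched to sorafenib patients, whereas the calculation uses all patients by diagnosis-year quota. These points change the size but not the direction. Even sorafenib patients diagnosed before 2008 can have at most about 4 years from starting sorafenib in 2008 or later.

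**Adverse events may be little affected.** This is right if time on treatment is short, as the 0.25-year row shows. The article gives no figure to settle it.

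**Concurrent controls share the calendar window.** This is also right. A reader might infer that every sorafenib comparison is distorted. Within 2008–2011 the bias arises only if treatment start dates differ between therapies, and the article does not show that they do.

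**The end points are secondary.** Overall survival and progression are assigned to Cox models, and the article concedes that comparisons are not randomised. This lowers the severity. It does not answer the point, because unequal follow-up is a separate problem from non-randomised allocation.

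**Conclusion.** The concern holds for the historic-control comparison. The logistic odds ratios there are confounded by follow-up length, in favour of the later period. It would go too far to say that they measure nothing but follow-up: a true difference still moves them, but it can be swamped or reversed.

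For treatment failure the distortion is large: an odds ratio of about 0.01 to 0.3 under equal risk, for median times to failure of 0.5 to 5 years (0.11 at 0.5 per year). For treatment-limiting adverse events it ranges from negligible (about 0.95) to substantial (about 0.4), depending on time on treatment.

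These sizes rest on constant and equal hazards, evenly spread diagnoses, the stated quotas and full administrative follow-up. Heavy loss would bring the treatment failure figure closer to 1. The primary end point and progression are not touched by this point. It should be fixed before analysis.

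**What to change.** In Data analysis, analyse both end points with the time-to definitions already in Table 1:

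- **Treatment failure:** a Cox model for time to treatment failure.
- **Treatment-limiting adverse events:** a cause-specific Cox model with cumulative incidence curves, treating death and introduction of other therapy as competing events.

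If a yes/no summary is kept, count events within one fixed window from treatment start. Restrict it to patients whose treatment began early enough to complete the window before 31 December 2011. A window that fits within follow-up from diagnosis is not enough, because treatment may start later. With a common window the odds ratio is 1 when risk is equal. With six months and a true hazard ratio of 0.7, it is 0.63, 0.66 and 0.68 for median times to failure of 0.5, 1 and 2 years.

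The cost is a change of wording. The times and censoring rules are already defined in Table 1, so no new end point is needed.

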### Data collection

The following data will be systematically collected for all enrolled patients: (1) date of diagnosis and/or date of first HCC visit; (2) demographic and clinical characteristics at the time of diagnosis/first HCC visit and at all occurrences of new treatment intervention during the study period via medical chart review; (3) data on variants of HCC diagnosis, for example, mixed HCC, fibrolamellar HCC, and on the additional diagnosis of cholangiocarcinoma; (4) data on the use of currently available HCC treatment approaches during the study period from medical chart review; (5) data on the use of new treatments for HCC if they become available and are used prior to study end; (6) data on hospitalizations, clinical visits, and visits to other health care professionals, with collection of hepatic function, tumor assessments, and laboratory values according to clinical judgment; and (7) data on method of payment for health care utilization. All data will be collected retrospectively and prospectively at study sites in order to account for patient records over the full duration of the study; data collection is expected to be complete by June 2012. All sites will enter data into an electronic data capture system developed by Outcome Sciences, Inc. (Cambridge, MA, USA). Outcome Sciences will manage the data system, including monthly data monitoring and cleaning, site queries, and check of invalid clinical values determined a priori by study investigators. All data collection procedures will comply with Chinese privacy and confidentiality requirements.

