**Health care access**
• Evaluation of the level of health care access in different regions/provinces and association with clinical outcomes
• Examination of any potential influence of immigrant/minority status, risk factor status, and alcohol and drug use on health care access

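### Method of payment is collected but is neither a matching variable nor a listed model covariate for the sorafenib comparison, so payment differences may be credited to sorafenib

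*Protocol article*

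**What the plan says.** Four parts of the protocol article bear on this point.

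- **Data collection** lists, among the items gathered for all enrolled patients, "data on method of payment for health care utilization". It gives no time point for this item. Demographic and clinical characteristics, by contrast, are tied to diagnosis or first visit and to each new treatment.
- **Comparator groups** describes how historic controls are paired with sorafenib patients: "statistically matched within the pool of patient data by age, sex, Child-Pugh status, and HCC stage". That is four variables, none of them about payment or access.
- **Data analysis** fixes the adjustment: "Covariates for the models will include disease stage, gender, age, duration of disease, etiology of disease, liver status, tumor size/spread". The same sentence goes on to name the remaining factors and the level of analysis: "surgical intervention/number of interventions, and number of comorbidities; analyses will be conducted at the site and country level". On the sorafenib comparison, the section has this to say: "The same analysis plan will be adopted for the evaluation of survival and other clinical end points with sorafenib versus other therapies". The one difference is that treatment enters the model. No other section adds payment.
- **Table 2, Health care access**, includes "Evaluation of the level of health care access in different regions/provinces and association with clinical outcomes". The table's caption describes its contents as "Additional aspects of HCC management for potential evaluation using data from the HCC BRIDGE China national study".

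**The concern.** Sorafenib is not assigned at random here, so the comparison rests on matching and on covariates. Both lists contain only clinical and demographic factors. How care is paid for could plausibly affect who receives a newly available drug. It could also affect survival through the rest of a patient's care. A variable that does both is a confounder, and disease stage and Child-Pugh status do not stand in for it.

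The historic-control comparison is exposed in a particular way. Patients in the earlier period could not receive sorafenib, so that pool is not selected on ability to obtain it. The later sorafenib group is a treated subset. If payment influenced who entered that subset, matching on the four named variables would leave the imbalance in place. At stake is the hazard ratio for overall survival, the primary end point, in a comparison that the Background names as one of the two aims of the global study. The variable needed to check this is already being collected.

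**Working it through.** **1. Is payment used anywhere in the comparison?**

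- Collected for all patients: yes (Data collection).
- Among the matching variables: no, 0 of 4 (Comparator groups).
- Among the named model covariates: no (Data analysis).
- Added for the sorafenib models: no, only treatment is added (Data analysis).

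The omission is therefore confirmed from the text.

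**2. Does the site-level analysis deal with it?** In part. Estimates made within a site, together with the exclusion of patients living outside the site's province, remove differences in access between sites and regions. They do not remove differences between patients treated at the same site. Country-level analyses are planned as well.

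**3. How large could the effect be?** The article gives no payment distribution, no relation of payment to survival, no sorafenib share and no number of deaths, so there is no figure of the plan's own to reproduce. Every input below is an assumption.

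Let h be the mortality hazard ratio for better payment cover, and p1 and p0 the shares with better cover among sorafenib and comparison patients. Let the true sorafenib hazard ratio be 1.00, and let payment be unrelated to the adjusted covariates. Then approximately:

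apparent HR = (p1·h + 1 − p1) / (p0·h + 1 − p0)

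| p1 / p0 | h = 0.9 | h = 0.8 | h = 0.7 |
|---|---|---|---|
| 0.5 / 0.5 | 1.00 | 1.00 | 1.00 |
| 0.5 / 0.4 | 0.95/0.96 = 0.99 | 0.90/0.92 = 0.98 | 0.85/0.88 = 0.97 |
| 0.6 / 0.4 | 0.94/0.96 = 0.98 | 0.88/0.92 = 0.96 | 0.82/0.88 = 0.93 |
| 0.7 / 0.3 | 0.93/0.97 = 0.96 | 0.86/0.94 = 0.91 | 0.79/0.91 = 0.87 |

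The direction is assumed too. If better cover were less common among sorafenib patients, the ratio would exceed 1.

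**4. Would such a bias reach significance?** For D deaths and a share a on sorafenib, the expected z statistic is m = √(D·a·(1 − a))·ln(apparent HR). The two-sided rejection rate is Φ(−m − 1.96) + Φ(m − 1.96). The article sets the 0.05 level; two-sided testing is assumed.

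With D = 2000 and a = 0.10 (both assumed), √(2000 × 0.10 × 0.90) = 13.42.

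- Apparent HR 1.00: rejection 0.05, the nominal level.
- 0.6 / 0.4 with h = 0.8 (HR 0.957): rejection 0.09.
- 0.7 / 0.3 with h = 0.7 (HR 0.868): m = 13.42 × (−0.141) = −1.90, rejection 0.48.

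The last case moves from 0.27 with 1000 deaths to 0.77 with 4000 deaths, at the same 10% share. The answer thus depends on deaths and on the sorafenib share, neither of which is stated.

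**5. After adjustment.** If payment were measured without error and modelled, this component of bias would vanish: apparent HR 1.00, rejection 0.05.

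**The case against.** The other side has several good points.

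- **A reader might infer that the authors expect access to affect outcome.** The documents do not say so. Table 2 lists the association as a potential evaluation, at the level of region or province rather than of the individual patient's payment.
- **A reader might infer that differences in patients' means are in fact credited to sorafenib.** That needs payment to differ between the groups after adjustment and also to relate to survival. No section states either. The Background says that treatment choice generally follows liver function and tumour burden, and both are adjusted for. Only the conditional statement is supported.
- **A reader might infer that the large enrolment would make such a bias significant.** Precision depends on deaths and on the share treated with sorafenib. In most of the assumed cases with 2000 deaths and a 10% share, the rejection rate stays well below one half.
- **The covariate list is not strictly closed, and the article condenses a fuller protocol.** This is fair, but the article chose to name four matching variables and a long, specific covariate list. Payment is in neither.
- **The Discussion already concedes the lack of randomization and differences in quality of care between centers.** It does so in general terms. A general caveat is no reason to leave a collected variable unused.
- **A baseline payment covariate may not exist.** This stands. The payment item has no stated time point, and the fix must allow for that.
- **Matching on a fifth variable could shrink the pool of matches**, with only 100 historic controls planned per site. This also stands, and it argues for a model covariate instead.

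**Conclusion.** The point holds in conditional form. A collected variable that could plausibly confound treatment choice and survival is absent from both the matching and the named covariates of the sorafenib comparison, and site-level analysis does not remove patient-level differences within a site. Whether it biases the result, and by how much, cannot be derived from the documents. Under the ranges assumed above, a null effect would appear as a hazard ratio between 1.00 and about 0.87. These figures rest on a single binary payment variable that is unrelated to the adjusted covariates and more often favourable among sorafenib patients. The change is worth making because it is cheap and the comparison is central, not because a bias has been shown.

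**What to change.** Add method of payment as a covariate in the Cox and logistic models for sorafenib versus other therapies, including the analysis of the matched historic-control set. Use the record nearest the start of the index treatment, and state in advance whether missing values form their own category or are imputed. If payment is not entered in the main models, prespecify a sensitivity analysis that includes it. Do not require it as an additional matching variable.

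The cost is one variable already on the data collection list and a line or two in the analysis plan. Two drawbacks need attention. Payment may be poorly recorded for some patients, particularly those from 2005-2007. The date to which each payment record refers must also be confirmed, because a record made after treatment began may reflect the treatment itself.
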